## **“Physical and mental pleasure”**

# **Effects of a Mutual Recovery Intervention on Mental Health in Depressed Elderly Community-dwelling Adults: a Pilot Study**

## **Abstract**

**Objective:** To examine the effects of mutual recovery program intervention in older adults with high risk of depression at communities in Shanghai, explore suitable approaches to improve mental health of community elders and provide basis for future policy making.

**Methods/Design:** The study involves a cluster-randomized controlled trial. Recruitment were completed between July 2012 and August 2012. Using a, we randomize 6 communities (N=237) into either the intervention group (3 communities, n=105) or to a wait-list control group (3 communities, n=132). All participants should meet screening criteria of depression, which is defined by The Geriatric Depression Scale (GDS-15). From March 2013 to May 2013, participants in the intervention group will receive a two-month mutual recovery program intervention, including 7 ninety-minutes, weekly sessions, which are based on a standardized self-designed schedule.

**Discussion:** Mutual recovery is a comprehensive and inexpensive approach for mental health intervention and could be a creative and helpful strategy to promote the mental health in older adults with high risk of depression at communities.

**Keywords:** Depression; Well-being; Community Intervention; Mental Health; Elderly; Cluster Randomized Trial

# Background

The proportion of elder adults (8.3% for 65 and over) are being one of the largest segments of Chinese population. The number has already reached 110 million, which is also the largest in the world [1, 2]. In the meanwhile, as the common disease among older adults which cost almost 80 billion dollars per year in China [3], nearly 10% of community elders and 15% to 25% of hospitalized ones are suffering major depression disorders [4]. And the proportion would reach to 35% if the mild depression was figured in [5]. According to the data of World Health Organization, depression is now the fourth-largest burden on disease cost in the world and will be the second in 2020 [6-9]. Mutual recovery is a comprehensive and inexpensive approach for mental health intervention [10]. Among various kinds of intervention programs which have been used to address the problem, cognitive behavior therapy (CBT) is usually used but results are mixed [11-13]. Conventional CBT is delivered face-to-face, meaning that the limited community resources which need to provide to everyone that would potentially benefit for depression will be less [13, 14]. Although the efficiency of CBT is reliable during face-to-face or group teaching procedures, it lacks of interaction and communication within participants and facilitators [15]. And counseling, an effective treatment for depression in population, is not flexible for older depression as it is inaccessible for the elders and inapprehensible because of the barriers between their generations [16].

Facing the growing burden of depression, innovative paradigms of intervention are needed to overcome the weakness as emerged in previous study [17]. The notion of recovering an initiative life and cultivating positive social and communal connections and relationships and well-being through mutual practices and relationships, and participating is gaining increasing concern and support [18, 19]. Mutual recovery focus on mutuality or reciprocity that would benefit anyone who involves in the process of intervention [19-21]. Participants in mutual recovery group will have chance to interact and communicate the contents taught in the session, as well as any interesting topic out

of the session as deeper and deeper connections would be made during the mutual recovery process and an ongoing self-administration mechanism for depression might be activated [22]. And as many commentators remarked that mental health have often been consolidated in strongly individualistic terms [23], the mutual recovery opens up new possibilities for the goodness by sharing their practices and thoughts. Furthermore, during the communication and interaction with participants, the facilitators also have chances to get the feedback about their intervention and refine the schedule all through the total sessions for a better outcome. In addition, music and story sharing, which create opportunities for breaking silence in a supportive environment, were used as an icebreaking tool for expressing and understanding experiences and emotions and persuading new and better identities and communities [24, 25]. It could be a tool for the facilitator to introduce and start the topic and could be a way to lessen their vigilance [24]. The advantages of the main kind of mental health intervention, like CBT [11], problem solving [26], physical activity [27, 28] and relaxing therapy, were also utilized in the session.

Therefore, we developed a mutual recovery intervention based on culture of China and conducted a series of training courses communities in Pudong, Shanghai. We will examine the outcomes and effects of this kind of intervention among older adults with high risk of depression.

## **Aims and Hypothesis**

The principal research purpose is to examine the effects of mutual recovery program intervention in older adults with high risk of depression at communities in Shanghai. Further, the aim of this study is to explore suitable approaches to improve mental health of community elders and provide basis for future policy making.

## **Methods**

## **Design overview**

The study is a two-armed cluster-randomized wait-list controlled trial. Recruitment will be completed between July 2012 and August 2012. Participants are recruited from six communities, which is randomly selected from 24 communities in Pudong district, Shanghai. In order to organize better and reduce potential confounding factors, each community is assigned an unique number for randomization. Using (Predictive Analytics Software, PASW) 18.0 for Windows Random Sampling, six communities are randomized into to either the mutual recovery intervention or wait-list control group. To ensure the effect of the mutual recovery program and take full advantage of the local resources, intervention communities are divided into several subgroups, each containing 15 to 20 participants, based on interpersonal relationships and shared interests, with two prestigious participants as leaders respectively. The intervention group will receive a two-month mutual recovery program intervention, including 7 ninety-minutes, weekly sessions, which are based on a standardized self-designed schedule. Participants in the wait-list group will also receive the intervention one year later. A baseline survey (T1) will be conducted with both the intervention and wait-list control group 6 months before the intervention. The survey will be conducted again right before the intervention began (T2) and immediately after the sessions (T3). Follow-up information will be collected weekly from the subgroup leaders by phone call to record the mental health change process of every participant in mutual recovery program groups

## **Population**

Participants will be selected by following inclusion criteria: (a) age ranged from 50 to 80; (b) no life-threatening illness; (c) ability to read and self-report; (d) no serious concurrent psychological or psychiatric disease or other physical disease that impact physical activities or mental health; (e) no outing in recent period; (f) a diagnosis of Geriatric Depression Scale 15 scoring 5 or more; (g) absence of apparent cognitive impairment as checked by a score of 8 or higher on the Mental Status Questionnaire

(Kahn, 1960).

## **Intervention**

The intervention group will receive a two-month mutual recovery program intervention, including 7 ninety-minutes, weekly sessions, which are based on a standardized self-designed schedule.

A toolkit will be provided to them, containing:

- (a) A note book to do their homework and record any question in utilizing the session skills or contents;
- (b) A self-administered mental health manual which is in step with the intervention session;
- (c) A follow-up list, which is only given to the leaders of subgroup weekly.

These sessions are assorted with the self-administered mental health manual, and they maybe not on a standardized but flexible fashion depending on the different needs from different subgroups. A seminar room will be provided for the sessions in each community and all subgroup sessions will be conducted by the same facilitator, the core member of designing the self-administered mental health manual and self-designed intervention schedule.

The intervention schedule is detailed below:

- (i) Self-introduction; general introduction of mental health, especially depression; activities of “destined acquaintance” to pair up all the group members, session overview.
- (ii) Develop a plan of the relaxation exercise; meditate or practice deep breathing; correct the cognitive distortions and fight against negative thinking.
- (iii) Emotion Management and problem solving; introduce the technique steps to solve the problem and make concrete plans.
- (iv) Self-regulation of Insomnia; introduce the relation between sleep and health; make plans of sleep health.

- (v) Diet and health; introduce a balanced diet tailored for the elderly and depression;
- (vi) Physical activity and health; make them understand how to exercise scientifically and decide a rationale plan of daily activity.
- (vii) Summary and commendation; exchanging and sharing

Music, story, and game are used alternately in the intervention sessions to active atmosphere, promote communication and facilitate practice.

- Music: Each subgroup have chances to select their interested song or music, which will be played before each session and during the partner discussion.
- Homework sharing: to begin each session, homework of the last session should be discussed first is also a process of problem solving.
- Game time: games are arranged in the middle of each session to make participants keep excited in learning.
- Story discussion: short allegory, closely related to the theme that is being taught on each session, is arranged for participants to discuss and interact before theoretic knowledge is conducted. In the process of discussion, participants may get a better understanding of the following topic.

### **Intervention characteristics**

- The toolkit is tailored to the community elderly, meeting the actual needs of them. The content of the handbook is easy understanding and the course is interesting and vivid.
- Participants play a major role in the process of intervention under the teacher's guide.
- Emphasis on homework and experience sharing. To begin each session, homework of the last session should be discussed first is also a process of problem solving.
- Teach through lively activities. For example, "Health ten clap" and "Quick reaction test" and "Ice breaking game" are used to facilitate communication and increase people's interest.

- Phone call following-up. Follow-up information is collected weekly from the subgroup leaders by phone call to record the mental health change process of every participant in mutual recovery program groups
- Evaluation will be conducted during the whole program: six months before intervention, right before intervention and after intervention and weekly following-up through phone call.

## **Ethical Permission**

Written Informed Consent Statement Forms will be obtained from the respondents. The right to withdraw and autonomy of the respondents will be explained. For ethical reasons, after first round of intervention is completed, the mutual recovery intervention will be provided to the wait-list control group. The study has received ethical permission from the ethics committee of School of Public Health of Fudan University, China 51 (IRB00002408&FWA00002399).

## **Data collection and Measure**

A baseline survey (T1) will be conducted with both the intervention and wait-list control group 6 months before the intervention. The survey will be conducted again right before the intervention began (T2) and immediately after the sessions (T3). Follow-up information will be collected weekly from the subgroup leaders by phone call to record the mental health change process of every participant in mutual recovery program groups

- **Demographic characteristics**

Including sex, age, marriage status, previous occupation, educational level and so on.

- **Self-reported health**

Height, weight, blood pressure, general health, self-reported chronic disease, smoking, drinking and physical activity.

- **Geriatric Depression Scale-15(GDS-15)**

GDS-15 is used to evaluate depressive risk severity at baseline. GDS-15 contains 15

items to assess depression especially of older adults, using a yes/no answer format. The original GDS have 30 items and the initial validation study indicated high internal consistency, with alpha of 0.94, and high convergent validity, as indicated by a correlation of 0.83 with Hamilton Rating Scale for Depression (HRSD), which suggested a cut-point of 5, with scores of 5 or higher indicative of depression.

- **WHO5 Well-being Index (WHO5)**

WHO5 is used to assess life satisfaction and depression severity. It is initially developed by Bech. P in 1998, then revised and recommended to assess life satisfaction by the psychology research collaboration center of the World Health Organization. It is translated into Chinese and introduced to China in 2004 with acceptable internal consistency and validity. There are 5 items in this scale, using a likert 6 rating format from 0 to 5, and usually the replier would be located as good life satisfaction when scoring over the cut-point of 13.

- **Self-administered Insomnia Questionnaire (SIQ)**

Sleep condition is assessed by Self-administered Insomnia Questionnaire which uses likert 5 rating format, from 1 to 5, and includes 3 items describing 3 aspects of the sleep process, such as: (a) taking a long time to fall asleep; (b) cannot stay asleep; (c) wake up too early. It would be judged as insomnia when any one of the 3 items is positive.

Self-made general demographic questionnaire, including the information of gender, age, marriage, education and pre-work position, is used to control the general study condition and specify the suitable people if this program is going to be generalized in the future.

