## **Data analysis**

PASW 18.0 for Windows will be used for data analysis. Pearson Chi-square test will be conducted to compare the two groups on difference of the classified data on 3 assessments. A multivariate ANOVA will be conducted to explore the differences within groups, at each of the 3 testing points, on the measures of sleep, WHO5 and

GDS-15. A series of repeated measures ANOVAs will be conducted to compare the two groups on all the variables tested across the screening, pretesting and post testing assessments. This approach is flexible and it is possible to model the dependence between observations from the same individual. Multilevel models can be applied to normally distributed and non-normally distributed outcomes; we will choose the most appropriate model based on the data.

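### No primary outcome, time point or contrast is named, and GDS-15 is described as a baseline measure in one section but analysed at all three surveys in another

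*Protocol*

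**What the plan says.** - **Aim** (Protocol, Aims and Hypothesis): "The principal research purpose is to examine the effects of mutual recovery program intervention in older adults with high risk of depression". No measure, time point or contrast follows, and no hypothesis is stated under that heading.
- **GDS-15** (Data collection and Measure): "GDS-15 is used to evaluate depressive risk severity at baseline". It is also the entry criterion in Population: "a diagnosis of Geriatric Depression Scale 15 scoring 5 or more".
- **WHO5** (Data collection and Measure): "WHO5 is used to assess life satisfaction and depression severity". A cut-point of 13 is given.
- **Sleep** (SIQ, same section): three items, with a yes/no rule: "It would be judged as insomnia when any one of the 3 items is positive".
- **Analysis** (Data analysis): a multivariate ANOVA of differences within groups is planned "at each of the 3 testing points, on the measures of sleep, WHO5 and" GDS-15. The arms are compared in two ways. For categories, "Pearson Chi-square test will be conducted to compare the two groups on difference of the classified data on 3 assessments". For the measures, "A series of repeated measures ANOVAs will be conducted to compare the two groups on all the variables tested". The section ends by leaving the choice of model until the data are in hand.

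No alpha, power or sample-size calculation is given. The title calls the study a pilot, while the aims include informing future policy.

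**The concern.** A primary outcome belongs in the protocol because it fixes what the trial may conclude. Here three scales stand level, each can be read as a score or as a category, and nothing says which one carries the claim. If GDS-15 and WHO5 disagree at T3, the protocol gives no basis for saying what was shown about depression. The sentence tying GDS-15 to baseline makes this worse: read literally, it turns the obvious depression endpoint into a screening tool.

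The contrast is open too. A repeated measures ANOVA over T1, T2 and T3 yields a group effect and a group-by-time interaction. Two of the three surveys precede the intervention, so these effects answer different questions, and the protocol does not say which is the treatment effect.

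**Working it through.** **Text check.** Data collection and Measure places GDS-15 at baseline. The same section says the survey is repeated at T2 and T3, and Data analysis includes GDS-15 at every testing point. The baseline sentence is therefore at odds with the analysis plan. WHO5 and GDS-15 overlap on depression severity, and neither is named as the depression endpoint. The multivariate ANOVA cannot act as a gatekeeper for the between-arm tests, because it is described as looking within groups.

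**Inputs.**
- Measures compared between arms: 3 (GDS-15, WHO5, sleep), from Data analysis.
- If each is also tested as a category after the intervention: 3 × 2 = 6 tests. This is a reading of the chi-square sentence, which does not define its categories.
- Alpha per test: 0.05 two-sided. This is an assumption; the protocol states none.
- Correlation between test statistics: not given, so varied from 0 to 0.9.

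There is no design error rate to reproduce. The only arithmetic in the text, 105 + 132 = 237, agrees.

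**Independent tests.**
- Three measures: 1 − 0.95³ = 1 − 0.8574 = 14.3%.
- Six tests: 1 − 0.95⁶ = 1 − 0.7351 = 26.5%.
- Three measures, favourable direction only: 1 − 0.975³ = 1 − 0.9269 = 7.3%, against 2.5% for one test.

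**Correlated tests.** Each statistic was simulated as Z = √ρ·C + √(1−ρ)·E, with C shared, E specific to the test, and one million draws. A false positive is any |Z| > 1.96, or any Z > 1.96 for the favourable direction.

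| Correlation | 3 measures, two-sided | 3 measures, favourable only | 6 tests, two-sided |
|---|---|---|---|
| 0 | 14.3% | 7.3% | 26.5% |
| 0.3 | 13.6% | 6.8% | 24.2% |
| 0.5 | 12.6% | 6.3% | 20.7% |
| 0.7 | 10.9% | 5.5% | 16.4% |
| 0.9 | 8.4% | 4.2% | 10.8% |

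**Cross-check.** A separate simulation drew outcomes for 105 and 132 participants and ran t-tests at one time point. It gave 12.4%, 12.5% and 10.3% at correlations 0.3, 0.5 and 0.7. Adding a median-split chi-square for each outcome gave 20.4%, 20.5% and 16.6%. Median splits are not the protocol's cut-points, so this supports the order of magnitude only.

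**After a fix.** One designated outcome tested at 0.05 has an error rate of 5%. Three co-primary measures at 0.05/3 = 0.0167 each give 1 − (1 − 0.0167)³ = 4.9% if independent.

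**The case against.** The strongest reply is that the text is loose rather than wrong. The baseline sentence does not say GDS-15 is used only then, and the survey is plainly repeated. A reader might infer that GDS-15 is not collected after baseline; the documents do not support that, and the sentence needs only a small correction. Likewise, a reader might call the WHO5 role a contradiction. It is an overlap: two scales may both bear on depression severity, but the protocol should say which one decides.

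A reader might also infer that every test is run at an unadjusted 5% level. No level is stated, and a multiplicity rule may sit in an analysis plan that is not shown. Its absence here is not a finding, and a particular correction for the secondary measures is a matter of preference.

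A reader might count nine chi-square tests (three measures at three surveys) plus three ANOVAs and quote 1 − 0.95¹² = 46%. That does not hold as the risk of a false efficacy claim. Six of the nine chi-square tests fall at T1 and T2, before any intervention. If T1 is the screening survey, everyone scores 5 or more on GDS-15 at that point, so that category cannot vary.

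Finally, the error rates do not model the planned repeated measures ANOVAs exactly, and the pilot label weakens the demand for confirmatory rigour. Both points stand and limit the size and weight of the finding. Neither supplies a primary outcome.

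**Conclusion.** The point holds. The protocol designates no primary outcome, time point or contrast, plans unranked between-arm comparisons, and describes the role of GDS-15 inconsistently with its own analysis. Followed as written, any of three scales can carry the conclusion.

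The inflation is moderate: about 8% to 14% for three measures, and about 11% to 26% if each is also tested as a category. In the favourable direction alone it is about 4% to 7% for three measures against 2.5%. These sizes rest on the assumed alpha and correlations. They leave out clustering by community and the open choice of model.

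The pilot label lowers the severity. It does not dispose of the point, because the stated purpose is to examine effects and inform policy, and the analysis consists of between-arm tests rather than feasibility estimates.

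**What to change.** Before analysis:

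1. Name one primary outcome, time point and contrast. The between-arm difference in GDS-15 score at T3, adjusted for the T2 score, fits the entry criterion and the depression focus, and T2 is the last survey before the intervention. The protocol does not itself dictate this choice; what matters is that one is fixed.
2. Correct the GDS-15 sentence in Data collection and Measure to say that the scale is measured at T1, T2 and T3.
3. Label WHO5, SIQ and all dichotomised versions, including GDS-15 at its cut-point, as secondary or exploratory. How they are adjusted, if at all, can be left to the analysis plan.

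All of this uses data already planned, so the cost is wording. The downside is that claims on WHO5, sleep and the categorical versions become weaker.

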## **Data analysis**

PASW 18.0 for Windows will be used for data analysis. Pearson Chi-square test will be conducted to compare the two groups on difference of the classified data on 3 assessments. A multivariate ANOVA will be conducted to explore the differences within groups, at each of the 3 testing points, on the measures of sleep, WHO5 and

GDS-15. A series of repeated measures ANOVAs will be conducted to compare the two groups on all the variables tested across the screening, pretesting and post testing assessments. This approach is flexible and it is possible to model the dependence between observations from the same individual. Multilevel models can be applied to normally distributed and non-normally distributed outcomes; we will choose the most appropriate model based on the data.

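### The planned Pearson chi-square at T1, T2 and T3 is undefined for the GDS-15 class at T1, cannot show a treatment effect before T3, and at T3 ignores that only six communities were randomised

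*Protocol*

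**What the plan says.** The Protocol, Data analysis, plans a between-group test at every assessment: "Pearson Chi-square test will be conducted to compare the two groups on difference of the classified data on 3 assessments". It does not list the variables. The same paragraph plans a multivariate ANOVA and a series of repeated measures ANOVAs on the scales, and says that multilevel models may be used. The dependence it mentions is between observations on one person; community is not mentioned there.

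Data collection and Measure gives one class per scale:

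- GDS-15: "with scores of 5 or higher indicative of depression"
- WHO5: "good life satisfaction when scoring over the cut-point of 13"
- Sleep questionnaire (SIQ), items scored 1 to 5: "It would be judged as insomnia when any one of the 3 items is positive"

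Population, criterion (f), requires for entry "a diagnosis of Geriatric Depression Scale 15 scoring 5 or more". Data analysis calls the first of the three assessments the screening assessment. Design overview places T1 six months before the intervention, T2 right before it and T3 straight after the sessions.

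The Abstract gives the units and numbers: "randomize 6 communities (N=237) into either the intervention group (3 communities, n=105) or to a wait-list control group (3 communities, n=132". The Discussion confirms that communities, not individuals, are randomised.

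**The concern.** One sentence applies the same test at three time points that differ in what they can show. At T1 the entry rule fixes one of the classes. At T1 and T2 no one has been treated. T3 is the only assessment after the intervention, and there the test uses neither the full score nor the T2 measurement of the same person.

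The more serious matter is the unit of analysis. A Pearson chi-square assumes independent observations. People in one community share a neighbourhood, local conditions and, in the intervention arm, subgroups that meet together. If outcomes are even slightly alike within communities, the chi-square understates the variance of the difference between arms. A chance difference between two sets of three communities could then be reported as an effect of the programme.

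**Working it through.** **Inputs from the Protocol.** 105 and 132 participants (105 + 132 = 237); 3 communities per arm; GDS-15 of 5 or more both for entry and for the class; T1 and T2 before the intervention, T3 after. The Protocol gives no sample-size calculation, error level or ICC, so there is no figure to reproduce.

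**Assumptions.** Two-sided 0.05; ICC 0.01 to 0.10; communities of equal size within an arm (105/3 = 35 and 132/3 = 44); no dropout.

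**Step 1: GDS-15 class at T1.** If T1 is the screening assessment, everyone scores 5 or more:

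| | 5 or more | below 5 |
|---|---|---|
| Intervention | 105 | 0 |
| Wait-list | 132 | 0 |

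Expected count = row total × column total / 237. In the second column this is 105 × 0/237 = 0 and 132 × 0/237 = 0. Each of those cells contributes (0 − 0)²/0, so the statistic is undefined.

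**Step 2: what the tests can show.** Three scale classes at three assessments make 9 tests. Six fall at T1 or T2. One of the six is undefined (step 1); the other five can be computed but compare arms before treatment. Three fall at T3.

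**Step 3: error of the T3 test under clustering.** For a 2 × 2 table the Pearson statistic is the square of z = (p1 − p2)/√[p(1 − p)(1/105 + 1/132)]. With clustering, each arm's variance is multiplied by its design effect, 1 + (m − 1) × ICC, with m = 35 or 44. With no treatment effect p(1 − p) cancels, and the true variance exceeds the assumed one by the factor

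R = (DE₁/105 + DE₂/132) / (1/105 + 1/132).

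The actual two-sided error is 2[1 − Φ(1.96/√R)].

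At ICC 0.05: DE₁ = 1 + 34 × 0.05 = 2.70 and DE₂ = 1 + 43 × 0.05 = 3.15. R = (0.02571 + 0.02386)/0.01710 = 2.90. 1.96/√2.90 = 1.15, and the error is 0.25.

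| Assumed ICC | DE₁ | DE₂ | R | Actual error at nominal 0.05 |
|---|---|---|---|---|
| 0.01 | 1.34 | 1.43 | 1.38 | 0.095 |
| 0.02 | 1.68 | 1.86 | 1.76 | 0.14 |
| 0.05 | 2.70 | 3.15 | 2.90 | 0.25 |
| 0.10 | 4.40 | 5.30 | 4.80 | 0.37 |

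**Step 4: information used at T3.** The class keeps only which side of a cut the person is on, and the test takes no account of the T2 score. The direction of the loss is certain. Its size depends on the effect, the SD, the correlation between assessments and the share above the cut, none of which the Protocol gives, so no figure is offered.

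**The case against.** Four objections deserve an answer, and each limits the point.

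*The variables are not named.* The term classified data could mean sex, education, smoking and similar items. This stands as a condition on steps 1 and 2. Still, Data collection and Measure defines a class for every scale, and re-testing sex or previous occupation at three assessments would make little sense, so the scale classes are the natural reading. Step 1 also needs T1 to be the screening assessment, as Data analysis implies. Even then, one scale at one time point is affected; a reader should not infer that T1 chi-square tests in general cannot be computed.

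*The scores are analysed anyway.* This stands. A reader might infer that the trial wastes power at T3. The documents do not support that: the repeated measures ANOVAs compare the groups on the same scales and can recover most of what dichotomising loses, and nothing makes the chi-square the primary test. But Data analysis does not rank the tests either, so an over-liberal chi-square result could be read as equal to the others.

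*Tests at T1 and T2 may still be informative.* A reader might infer that they merely test the randomisation. That is too strong: the Protocol does not fix whether communities were allocated before or after people were recruited and surveyed at T1. Differences could also reflect recruitment bias or, by T2, dropout or expectation. Describing the arms and reporting attrition serves those questions better than p-values, and none of them concerns the effect of treatment.

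*The insomnia threshold may be set elsewhere.* The rule does not say which value from 1 to 5 counts as positive. That detail may sit in the questionnaire or in an analysis plan not shown, so it is not a fault by itself. It matters here only because the class would be tested at T3 in a trial that the Discussion says cannot be blinded.

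The mention of multilevel models does not rescue the chi-square: it remains a separate individual-level test.

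**Conclusion.** The point holds in limited form. If the scale classes are among the variables tested, one of nine chi-square tests is undefined and five more precede the intervention. The three at T3 have an actual error of about 0.10 to 0.37 instead of 0.05 over an assumed ICC of 0.01 to 0.10, with equal communities within each arm; only at an ICC of zero is the nominal level kept. The clustering fault does not depend on which variables are meant: it applies to any individual-level outcome tested this way at T3.

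The loss of information from dichotomising is real, but it belongs to the chi-square alone and cannot be sized from the documents. The sentence should be changed because it adds an invalid test of the treatment effect, not because the trial depends on it.

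**What to change.** Replace the chi-square sentence in Data analysis with the following.

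- **T1 and T2:** describe both arms by community and overall, with no significance tests, and report losses between T1 and T2. Name the variables meant by classified data, and leave out the GDS-15 class at T1.
- **T3, lead analysis:** compare the GDS-15, WHO5 and SIQ scores between arms, adjusted for the T2 value, with a method that accounts for community and is valid for six clusters. Examples are a cluster-level analysis, or a mixed model with a small-sample correction. The score analysis needs this as much as the classes do, because a repeated measures ANOVA on individuals does not by itself handle community.
- **T3, supportive:** give the proportions by GDS-15, WHO5 and insomnia class from a cluster-adjusted analysis, with the SIQ item value that counts as positive fixed in numbers before T3 data are seen.

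The cost is wording and analysis time; no new data are needed, since T2 is already collected. Intervals will be wider, because six communities in two arms leave 6 − 2 = 4 degrees of freedom for an unadjusted cluster-level comparison. The simple percentages become supportive.
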